### Statistical aspects

#### Sample size

Preliminary data indicate that serum endotoxin levels in T2DM patients are two to three times higher than in control subjects. We hypothesize that treatment with probiotics will reduce mean endotoxin levels by 25 to 30%, while no change will be seen in the placebo group. To obtain 80% power to demonstrate a statistically significant difference (two-sided *P*-value = 0.05) between the two treatments, 100 patients must be treated (50 patients per group). As we expect a dropout rate of 15%, we will include 120 patients in the study.

The sample size was calculated based on the estimated mean change during treatment (Δ-values) and corresponding standard deviation (SD) of the change. Since we have no repeated measurements of endotoxin in the same individuals, we need to estimate the SD for the change. Assuming that the correlation between 1 and 2 yields a measurement of 0.70, the SD for the Δ-value is 78% of the SD of separate measurements (Table 2). Table 3 shows the estimated sample size according to various assumptions of treatment effect and correlation between one and two measurements.

**Table 2 T2:** Standard deviation and correlation between measures

**SD for each measurement**	**Correlation between measures**	**SD of the Δ-value**
1	0.60	0.89
1	0.65	0.84
1	0.70	0.78
1	0.75	0.71
1	0.80	0.63

Δ-value, mean change; SD, standard deviation.

**Table 3 T3:** Sample size determination for endotoxin

**Endotoxin baseline (U/L)**	**Difference in Δ-value (probiotics –placebo)**	**SD for change (common for both treatments)**	**Correlation for 1 and 2 measurements**	**Sample size (total) 2-tailed α: 0.05 Power: 80%**	**Sample size (total) 2-tailed α: 0.05 Power: 90%**
10 (± 6)	−2	5.34	0.60	224	298
	−2	5.04	0.65	200	266
	−2	4.68	0.70	176	236
	−2	4.26	0.75	148	198
	−2	3.78	0.80	116	154
	−2.5	5.34	0.60	144	192
	−2.5	5.04	0.65	128	172
	−2.5	4.68	0.70	114	152
	**−2.5**	**4.26**	**0.75**	**96**	**128**
	−2.5	3.78	0.80	76	100
	**−3**	**5.34**	**0.60**	**100**	**134**
	−3	5.04	0.65	90	120
	−3	4.68	0.70	80	106
	−3	4.26	0.75	68	90
	−3	3.78	0.80	54	70
	−4	5.34	0.60	58	76
	−4	5.04	0.65	52	68
	−4	4.68	0.70	46	62
	−4	4.26	0.75	40	52
	−4	3.78	0.80	32	40

Δ-value, mean change; SD, standard deviation.

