### Plan for data analysis

As this trial is designed to assess the physiological effects rather than support clinical indications for treatment with probiotic**s** in T2DM, we plan to perform per protocol analyses. Only subjects treated with at least 80% of the planned doses for at least 80% of the time will be considered as treated per protocol.

Raw data will be entered into statistical software (SPSS version 16.5, Chicago, IL, USA). Preparation of the dataset will be done prior to analysis. Descriptive statistics will be performed, and frequencies will be presented as a percentage. Continuous variables will be presented as mean ± SD. Variables exhibiting non-Gaussian variables will be transformed prior to analysis. Repeated measures analysis of co-variance will be used to compare groups, which will represent a combination of analysis of variance and linear regression. Confounding and fixed variables such as age and gender, as well as body mass index, will be taken if proper matching has not been achieved prior to repeated measures. *Post hoc* Banjamini-Hohberg corrections will be done for multiple comparisons. For comparison of two groups, an independent *t*-test will be applied for continuous variables and Mann–Whitney for non-continuous variables. Analysis of adverse events (if any) will be performed using Chi-Square test and Fisher’s exact test following assumptions of randomness, independence and size. Significance will be set at *P* < 0.05.

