
Taken together, the current evidence appears to support a role for the gut microbiota in the pathogenesis of diet-induced obesity and related metabolic disorders, which may be reversible with dietary and/or gut microbiota manipulation [50]. As the gut microbiota is the main source of endotoxin, treatment with probiotics may influence the circulating levels of endotoxin by altering the microbiota composition. To date, relatively few studies have examined the effects of endotoxin in metabolic diseases using probiotics. To the best of our knowledge, this hypothesis has not been tested except in a small study of patients with cirrhosis in which a 25% reduction in endotoxin was reported [1]. However, animal studies have revealed that treatment with probiotics may be beneficial in insulin-resistant states [2,37]. Probiotics also delay the onset of glucose intolerance in high-fructose-fed rats [3]. To expand on these earlier findings, the present study will explore the potential beneficial effects of probiotics on circulating endotoxin levels and other markers for systemic low-grade inflammation in patients with T2DM.

In summary, we expect that our findings will demonstrate that probiotics alter gut microbiota in T2DM and that, in theory, the alterations will be metabolically favorable with continued probiotic use. Since the efficacy of probiotics is directly linked to the type of strain, we will also be able to identify which strains used in the intervention are most beneficial for patients with T2DM. Further investigations, however, will be needed whether the efficacy of the probiotics used in this study can be extended to prevention levels. Regardless, our study will be the first to address this issue beyond classical inflammatory conditions. This will have a fundamental impact on how we should treat the inflammatory component of T2DM, particularly once the results are verified in a larger cohort of patients.

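### The 80% power claim for 100 patients does not match the one correlation the text names (0.70): at a 25% reduction, Table 3 asks for 114 and 100 give about 75%

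*Protocol article*

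**What the plan says.** All the design figures are in the protocol article, Statistical aspects, Sample size.

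- Effect: probiotics will "reduce mean endotoxin levels by 25 to 30%, while no change will be seen in the placebo group". Table 3 gives a baseline of 10 U/L with SD 6, so this is a difference in change of 2.5 to 3 U/L.
- Error rates: "To obtain 80% power to demonstrate a statistically significant difference", with "two-sided *P*-value = 0.05".
- Number: "100 patients must be treated (50 patients per group"). A 15% dropout rate raises this to 120 enrolled.
- Correlation: the authors have no repeated endotoxin measurements and must estimate the SD of change. They write: "Assuming that the correlation between 1 and 2 yields a measurement of 0.70, the SD for the Δ-value is 78% of the SD" of a single measurement. No other correlation appears in the text.
- Table 3 lists sample sizes for correlations from 0.60 to 0.80 and prints two rows in bold.

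Two other sections bear on the point. Plan for data analysis restricts the analysis: "Only subjects treated with at least 80% of the planned doses for at least 80% of the time" count as treated per protocol. The Discussion cites one human precedent for the effect, "a small study of patients with cirrhosis in which a 25% reduction in endotoxin was reported".

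**The concern.** A reader who takes the stated effect range and the stated correlation to Table 3 does not arrive at 100. The two figures there are 114 and 80. The bold rows come close to 100 only by pairing the smaller effect with a more favourable correlation than 0.70, and the larger effect with a less favourable one.

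The mismatch matters most at 25%. That is the lower end of the hypothesised range and also the only human effect figure the article cites. If the true reduction were 25% and the correlation 0.70, the chance of missing it would be about 25%, against the 20% that the text implies. A non-significant result should be read against the power that the stated assumptions actually give.

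**Working it through.** **Inputs, all from the Sample size section.** Two-sided alpha 0.05; equal groups of 50; baseline 10 U/L; single-measurement SD 6; correlation 0.70; SD of change 0.78 × 6 = 4.68; difference in change 2.5 to 3 U/L.

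**Step 1: reproduce the plan's figure.** The normal formula is n per group = 2 × (1.960 + 0.842)² × SD² / difference² = 15.70 × SD² / difference².

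- Bold row, 3 U/L with r = 0.60 (SD 5.34): 15.70 × 28.52 / 9 = 49.7, so 50 per group and 100 in total. This is the plan's number exactly. The t-distribution gives 102, and 50 per group give 80.2% power (normal) or 79.4% (t).
- Bold row, 2.5 U/L with r = 0.75 (SD 4.26): 15.70 × 18.15 / 6.25 = 45.6, so 46 per group and 92 in total (94 by t). Table 3 prints 96, slightly above the formula; this does not affect the point.
- Dropout: 100 / 0.85 = 117.6, so 118, which is consistent with 120.

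**Step 2: the same formula at the stated correlation (SD 4.68).**

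- 2.5 U/L: 15.70 × 21.90 / 6.25 = 55.01, so 56 per group and 112 in total (Table 3: 114).
- 3 U/L: 15.70 × 21.90 / 9 = 38.2, so 39 per group and 78 in total (80 by t; Table 3: 80).

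Neither end of the range gives 100.

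**Step 3: which correlation would support 100 over the whole range?** Totals printed in Table 3 for 80% power:

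| Correlation | 2.5 U/L (25%) | 3 U/L (30%) |
|---|---|---|
| 0.60 | 144 | **100** |
| 0.65 | 128 | 90 |
| 0.70 (text) | 114 | 80 |
| 0.75 | **96** | 68 |
| 0.80 | 76 | 54 |

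Among the tabulated values, 100 patients suffice from 25% to 30% only at 0.75 or above.

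**Step 4: power of 100 patients at r = 0.70.** The standard error is 4.68 × √(2/50) = 0.936. The non-centrality is difference / 0.936. Normal power is Φ(non-centrality − 1.960); the last column uses the noncentral t with 98 degrees of freedom.

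| Reduction | Difference (U/L) | Non-centrality | Power, normal | Power, t |
|---|---|---|---|---|
| 25% | 2.5 | 2.67 | 76.1% | 75.3% |
| 27.5% | 2.75 | 2.94 | 83.6% | 82.9% |
| 30% | 3.0 | 3.21 | 89.3% | 88.8% |

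The difference detectable with 80% power is 2.62 U/L (normal) or 0.566 × 4.68 = 2.65 U/L (t), a reduction of about 26 to 26.5%.

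**Step 5: sensitivity.** Without rounding the 0.78, the SD is 6 × √(2 × 0.30) = 4.65, and power at 25% is 75.9% (t). With the 120 × 0.85 = 102 patients left after dropout, it is 76.2% (t). Neither changes the conclusion.

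**Step 6: a baseline-adjusted comparison.** If baseline endotoxin were the covariate, the residual SD would be 6 × √(1 − 0.70²) = 4.285. At 2.5 U/L and 50 per group, power would be 82.3% (t) or 83.1% (normal).

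**The case against.** The strongest defence is that 100 was correctly computed. It is exactly the bold row at 3 U/L and r = 0.60, and the other bold row, at 2.5 U/L and r = 0.75, gives 96. On this reading the bold rows are the design scenarios, one at each end of the effect range, and 0.70 only illustrates how the SD of change is derived. This stands in part: it rules out a formula error. It does not remove the inconsistency, because 0.70 is the only correlation in the text, it is not labelled as an example, and the text does not explain the bold rows.

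A second defence is that 25% is the least favourable end of the range, taken from a small study in another disease. This also stands. At r = 0.70 the design exceeds 80% from about 26.5% upwards, which is most of the stated range.

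A third is that Plan for data analysis already names a repeated measures analysis of covariance, which could bring power above 80% at 25%. That depends on baseline endotoxin being a covariate, and the article does not say so. The sample size text rests expressly on change values, so the stated claim has to be judged on that basis.

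A reader might also infer that the 15% allowance leaves room for only two further losses (102 − 100), because non-adherent patients and those withdrawn for antibiotics leave the analysis as well. The document does not support this. It does not define dropout, nothing excludes those patients from the 15%, and the 100 treated patients may already be meant as the per-protocol number.

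**Conclusion.** The point holds as an inconsistency of moderate weight. The text claims 80% power for 25 to 30% and names r = 0.70. At that correlation, 100 evaluable patients deliver about 75% at the lower end, a shortfall of about 5 points that disappears at a reduction of about 26.5%.

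The figures assume a two-sample comparison of change scores, a baseline of 10 U/L with SD 6, equal SDs in both groups and 50 evaluable patients per group. The correlation is itself an assumption, and the result moves with it. At a 25% reduction, 100 patients give 64% power if r = 0.60 and 83% if r = 0.75.

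It would be tempting to conclude that the trial is underpowered, or that it must enrol 114 / 0.85 = 134.1, that is 135 patients. The documents do not support that. The number follows from one of the plan's own rows, it is adequate over most of the stated range even at r = 0.70, and a baseline-adjusted analysis could cover the rest.

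**What to change.** Keep 120 patients and make the sample size paragraph agree with itself in one of these ways.

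1. Restate the power at the stated correlation, for example: *With 100 evaluable patients and a correlation of 0.70, power is about 75% for a 25% reduction and 89% for a 30% reduction; 80% is reached at about 26.5%.*
2. Or name the single correlation and effect on which 100 rests, say why that correlation was chosen, and remove or explain the conflicting 0.70.
3. Or, if the primary comparison is to be adjusted for baseline endotoxin, say so and state power on that basis: about 82% at a 25% reduction, r = 0.70 and 100 evaluable patients. This replaces the 75% statement and should not appear beside it.

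Whichever is chosen, state that the 100 are patients evaluable per protocol, so that it is clear what the 15% allowance has to cover.

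The cost is a few sentences and no extra patients. Under option 1 the stated power at 25% becomes less favourable. Option 2 means defending one correlation without repeated-measures data. Option 3 commits the primary analysis to baseline as a covariate.

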### Plan for data analysis

As this trial is designed to assess the physiological effects rather than support clinical indications for treatment with probiotic**s** in T2DM, we plan to perform per protocol analyses. Only subjects treated with at least 80% of the planned doses for at least 80% of the time will be considered as treated per protocol.

Raw data will be entered into statistical software (SPSS version 16.5, Chicago, IL, USA). Preparation of the dataset will be done prior to analysis. Descriptive statistics will be performed, and frequencies will be presented as a percentage. Continuous variables will be presented as mean ± SD. Variables exhibiting non-Gaussian variables will be transformed prior to analysis. Repeated measures analysis of co-variance will be used to compare groups, which will represent a combination of analysis of variance and linear regression. Confounding and fixed variables such as age and gender, as well as body mass index, will be taken if proper matching has not been achieved prior to repeated measures. *Post hoc* Banjamini-Hohberg corrections will be done for multiple comparisons. For comparison of two groups, an independent *t*-test will be applied for continuous variables and Mann–Whitney for non-continuous variables. Analysis of adverse events (if any) will be performed using Chi-Square test and Fisher’s exact test following assumptions of randomness, independence and size. Significance will be set at *P* < 0.05.

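### Run as the classical model its wording describes, the planned repeated-measures ANCOVA drops every patient lacking a week-8 or week-26 sample; a mixed model on all randomised patients would use those data, with protection limited to missing-at-random

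*Protocol article*

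**What the plan says.** - **Method.** The protocol article, Plan for data analysis, says "Repeated measures analysis of co-variance will be used to compare groups". It explains the method as analysis of variance joined with linear regression. The software is SPSS: "Raw data will be entered into statistical software (SPSS version 16.5, Chicago, IL, USA". No estimation routine and no rule for missing samples is given.
- **Analysis set.** The same section says "we plan to perform per protocol analyses", because the aim is to study physiological effects. It then defines the set: "Only subjects treated with at least 80% of the planned doses for at least 80% of the time will be considered as treated per protocol". No other analysis set is named.
- **Samples.** Table 1 and the section on biochemical data and biological samples place fasting blood at weeks 0, 8 and 26, so each patient has two post-baseline endotoxin values.
- **Dropout.** Under Sample size, "100 patients must be treated (50 patients per group" for 80% power, and "As we expect a dropout rate of 15%, we will include 120 patients in the study". Enrolling more patients is the only provision for dropout.
- **Withdrawal.** Under Subject withdrawal, patients leave the study at their own request, for safety, behavioural or administrative reasons, or after specified antibiotic use.

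**The concern.** The plan names a method, so this is more than silence about missing data. Classical repeated-measures ANCOVA, in univariate or multivariate form, keeps only patients with a value at every time point. Someone who gives blood at week 8 and leaves before week 26 contributes nothing, not even to the week-8 comparison.

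Enrolling extra patients protects power but does not protect against selection. If those who leave differ in their earlier endotoxin values, and differ by arm, the completers no longer give a fair comparison. Systemic antibiotics are a reason for withdrawal and plausibly act on the gut flora under study, so completely random dropout is not a safe default. A likelihood-based mixed model uses the week-8 value of a patient who later leaves and needs no extra samples.

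**Working it through.** **1. The plan's own figures.** For a difference of -3 and an SD of change of 5.34 (a bold row of Table 3), the normal-approximation formula n per arm = 2 × (1.960 + 0.842)² × SD² / Δ² gives 2 × 7.849 × 28.52 / 9 = 49.7. That rounds to 50 per arm, or 100 in total, as stated. Enrolment: 100 / 0.85 = 117.6, so 118, against the stated 120. Expected completers: 120 × 0.85 = 102, or 51 per arm.

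**2. Power with 102 completers, 51 per arm.**

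| Bold row of Table 3 | Noncentral t | Normal approximation |
|---|---|---|
| Δ -3, SD 5.34 | 80.2% | 81.0% |
| Δ -2.5, SD 4.26 | 83.5% | 84.2% |

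The budget covers the expected dropout, so there is no power deficit to claim.

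**3. How many dropouts the per-protocol rule leaves.** Reading the rule as treatment for at least 80% of 26 weeks gives 0.8 × 26 = 20.8 weeks. Expected dropouts are 120 × 0.15 = 18. The stopping times are assumptions:
- Uniform over weeks 8 to 26: (26 - 20.8) / (26 - 8) = 0.289, and 18 × 0.289 = 5.2 stay in the set.
- Uniform over weeks 0 to 26: (26 - 20.8) / 26 = 0.20, and 18 × 0.20 = 3.6 stay in the set.

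The rule therefore removes most dropouts before any model is fitted.

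**4. Simulation of bias.** From the protocol: baseline 10, SD 6, correlation 0.70, 60 per arm, week-26 difference -3. Assumed: a week-8 difference of -1.5, the same correlation between all visits, all dropout after week 8, and uniform stopping times. Three mechanisms were used:
- MCAR: 15% at random in both arms.
- MAR: in the active arm, logit of dropout = 1.5 × (week-8 value - 10) / 6 - 1.75; in placebo, 15% at random. About 16% missing overall.
- MNAR: the same form driven by the unseen week-26 value, with intercept -1.4. About 16% missing.

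The complete-case estimate regresses week 26 on arm and baseline. The likelihood estimate factors the model into week 8 given baseline and week 26 given baseline and week 8. There were 6,000 replicates per mechanism. Mean estimated week-26 difference (truth -3.0):

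| Mechanism | Complete case | Likelihood, all randomised | Likelihood, per-protocol set |
|---|---|---|---|
| MCAR | -2.98 | -2.98 | -2.98 |
| MAR | -3.26 | -2.99 | -3.17 |
| MNAR | -3.63 | -3.53 | -3.59 |

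Under MAR the bias on the per-protocol set falls from 0.256 to 0.165, and (0.256 - 0.165) / 0.256 = 36%, about a third. On all randomised patients it essentially disappears. Under MCAR the standard error goes from 0.856 to 0.846, a gain of about 1%.

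**5. Direction and size.** Other runs with 15-17% dropout driven by week-8 values in one arm gave complete-case means of -2.57 or -3.40 against -3.0, and -3.04 or -3.00 from the mixed model on all randomised patients. The bias can go either way, depending on which arm loses its high values. In all these MAR runs it was 0.26 to 0.43, which is roughly a third to a half of a standard error of about 0.85.

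**The case against.** The strongest case against has four parts.

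- **The routine is not named.** Deletion belongs to a routine, not to the words repeated-measures ANCOVA. The named software also has a mixed-model procedure, and a separate analysis plan may settle the matter. This stands as a limit: the point is conditional on the classical routine. But that is the natural reading of a method described as analysis of variance with regression, and one line would remove the doubt.
- **The per-protocol rule acts first.** A reader might infer that a mixed model on the planned data would keep the 15% who drop out and protect the result. The documents do not support that. On the per-protocol set the model recovers only late dropouts and isolated missed samples. The benefit depends on adding a wider analysis set, which is a real change to a choice for which the plan gives a reason.
- **Protection is limited.** A reader might infer that the mixed model removes dropout bias in general. It does so only under missing-at-random. A patient lost before week 8 has no post-baseline value and adds almost nothing, and dropout linked to unseen values stays biased. The dropout mechanisms simulated here are constructed; treatment is double-blind, and nothing in the documents shows that endotoxin drives withdrawal.
- **Power.** A reader might infer a shortfall. The 15% is already budgeted, and any further loss would rest on an assumed rate of missed week-8 samples that the documents do not give.

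**Conclusion.** The point holds in a limited form. As worded, the planned analysis most naturally means a model that discards the observed week-8 value of every patient without a week-26 sample, and the reverse. Under the assumed week-8-driven dropout in one arm, at about the expected rate, this shifts the estimate by 0.26 to 0.43 on a true difference of 3.0, in either direction. A likelihood-based model removes nearly all of that on all randomised patients, but only about a third on the per-protocol set. It gains 1-2% in standard error under completely random dropout, and under MNAR a bias of 0.5 to 0.6 remains whichever method or set is used.

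The sample size and stated power are unaffected. The conclusion rests on the classical reading of the method, on the 20.8-week reading of the per-protocol rule, and on the assumed dropout mechanisms and stopping times.

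**What to change.** Replace the repeated-measures ANCOVA sentence with a likelihood-based linear mixed model:
- outcomes at weeks 8 and 26;
- baseline value, gender (the stratification factor), treatment, visit and treatment-by-visit as fixed effects;
- unstructured covariance across visits;
- the week-26 treatment contrast as the main result.

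Fit it to all randomised patients with any post-baseline sample. State openly that this set is in addition to the per-protocol set, which is kept and analysed with the same model. State the missing-at-random assumption, and say that early dropouts and dropout driven by unseen values are not corrected, so a sensitivity analysis for the latter is advisable.

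Cost: no new samples, visits or patients, and SPSS has a mixed-model procedure. The downside is a second analysis set to report and an explicit assumption to defend. This is a cheap improvement rather than a free one.

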### Allocation to treatment

After confirmation of eligibility and obtaining written informed consent, the patients will be given a unique subject number by the research nurse. The randomization (stratified for gender) will be performed by the probiotic company and the patients and clinicians at the primary care center will be blinded to the treatment received. The eligible patients will be allocated (1:1) to treatment for 26 weeks with either the probiotics supplement or placebo. Subjects will be instructed to:

•Ingest one sachet before breakfast and one sachet before going to bed, by mixing the powder in lukewarm water and drinking it.

•The sachets will be stored at room temperature.

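### Covariates enter the group comparison only if balance is judged inadequate, by no stated criterion; gender (the stratification factor) is left conditional and baseline endotoxin is not named

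*Protocol article*

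**What the plan says.** Four statements in the protocol article bear on this.

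- **Plan for data analysis, covariates.** Groups are compared by repeated measures ANCOVA. Age, gender and BMI are offered as examples of adjustment variables, and they "will be taken if proper matching has not been achieved prior to repeated measures". The list is open, and nothing says how matching is judged.
- **Plan for data analysis, second test.** An independent t-test (Mann–Whitney for non-continuous variables) is also listed for comparing two groups. The text does not say whether this or the ANCOVA gives the main endotoxin result.
- **Allocation to treatment.** "The randomization (stratified for gender) will be performed by the probiotic company".
- **Sample size.** "The sample size was calculated based on the estimated mean change during treatment", together with the SD of that change. The text takes a correlation of 0.70 between two measurements of the same patient. Baseline endotoxin is not named as a covariate there or in the analysis section.

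**The concern.** In a randomized trial, covariates are chosen because they predict the outcome or were used in the allocation, and they are fixed in advance. Here their inclusion depends on how the arms happen to look at baseline. That has three consequences.

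1. Because adequate matching is undefined and the list is open, two analysts could reach different models from the same data. With an unadjusted test listed alongside, the choice could follow the result.
2. Stratifying by gender makes gender imbalance unlikely. The one factor built into the allocation is therefore the one this rule would most often leave out.
3. Under the plan's own correlation assumptions, baseline endotoxin is a strong predictor of later endotoxin. If it is not in the model, precision already paid for in blood samples is lost.

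**Working it through.** **Inputs.** All are from the Sample size section and its Table 3: endotoxin 10 ± 6 U/L; a reduction of 25 to 30% against no change on placebo, so a difference of 2.5 to 3; "two-sided *P*-value = 0.05"; 80% power; 50 per group; r = 0.70 in the text, and r = 0.60 and 0.75 in the two bold rows of Table 3.

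**Step 1: the plan's own figure.** Bold row with difference 3, SD of change 5.34, r = 0.60, by normal approximation:

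n per arm = 2 × (1.960 + 0.842)² × (5.34/3)² ≈ 49.7, so 50 per arm and 100 in total. The stated 100 is reproduced.

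**Step 2: variance with and without baseline adjustment.** Let σ = 6 be the SD of one measurement.

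- Change score: variance 2σ²(1 − r)
- Baseline-adjusted ANCOVA: variance σ²(1 − r²)
- Ratio: (1 − r²) / [2(1 − r)] = (1 + r)/2

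**Step 3: power at 50 per arm** (two-sided t-test at 0.05, SDs from the formulas above, one follow-up):

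| Difference | r | Variance ratio | SD, change score | SD, ANCOVA | Power, change score | Power, ANCOVA |
|---|---|---|---|---|---|---|
| 2.5 | 0.70 | 0.85 | 4.65 | 4.28 | 75.9% | 82.3% |
| 3 | 0.60 | 0.80 | 5.37 | 4.80 | 79.0% | 87.2% |
| 2.5 | 0.75 | 0.875 | 4.24 | 3.97 | 83.1% | 87.7% |

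In the first row, the total N for 80% power is 112 with the change score and 96 with ANCOVA. The 79.0% in the second row is the plan's own 80%: the normal approximation with the tabulated SD of 5.34 gives 80.2%.

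The change-score column applies if baseline is handled as an ordinary repeated level. With one follow-up, the group-by-time test is then the same as the change-score test.

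**Step 4: type I error.** The document gives no trigger and no correlation of age, gender or BMI with endotoxin, so any simulation needs assumptions. These used 50 per arm, no treatment effect and, unless stated, baseline endotoxin as the covariate.

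- *Rule applied strictly*, adjusting only if a baseline test has P < 0.05 (assumed trigger): 3.2 to 4.7% rejections over r = 0.60 to 0.75, depending on whether the fallback is the follow-up value or the change score. With a weaker covariate (assumed r = 0.1 to 0.3) it was 4.7 to 4.9%. The rule is conservative or close to nominal.
- *Better of adjusted and unadjusted result*: 6.5 to 6.9% when the unadjusted result is the change score (r = 0.60 to 0.75), and 8.2% when it is the follow-up value (r = 0.70).

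**The case against.** **The ANCOVA may already adjust for baseline.** The article names analysis of covariance and describes it as combining analysis of variance with linear regression. Baseline endotoxin may be the intended covariate, or the full analysis plan may name it. Sizing on change scores and then analysing by ANCOVA would be conservative, not wrong. This stands, so the power gains above are conditional, and the silence on baseline is not itself an error. It does not rescue the conditional rule, which the article states outright.

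**A reader might infer that the balance rule inflates the false-positive rate.** The figures do not support that: applied strictly, it stays at or below 5%. The simulations also use baseline endotoxin and an assumed P < 0.05 trigger, neither of which is in the stated rule. The excess arises only if the analyst picks between results, and the document does not say that anyone will.

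**A reader might infer that the trial is underpowered for this reason.** That does not follow. The two bold rows of Table 3 support roughly 100 patients with change scores. The 76% figure pairs the text's r = 0.70 with the 25% effect, for which Table 3 lists 114. That mismatch is a separate sample-size matter.

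**Gender will be close to balanced anyway.** True, and no loss from omitting it can be computed from the document. The argument for including it is consistency with the stratified allocation.

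**A reader might want a log scale, or age and BMI forced in.** A mean of 10 with SD 6 and a percentage effect may suggest skewness but does not establish it, and the article already says: "Variables exhibiting non-Gaussian variables will be transformed prior to analysis". It gives no prognostic evidence for age or BMI.

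**Conclusion.** The concern holds for the rule as written: covariate inclusion triggered by balance, with no criterion and an open list, the stratification factor left conditional, and an unadjusted test listed without an order of precedence.

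- **Error rate.** No inflation if the rule is applied strictly. The exposure is about 6.5 to 8% if the better of two results is taken, assuming r between 0.60 and 0.75 and baseline endotoxin as the covariate. For weaker covariates the adjusted and unadjusted follow-up analyses nearly coincide, so switching between those two gains less.
- **Power.** About 5 to 8 percentage points at 50 per arm, only if baseline is not already the ANCOVA covariate and the alternative is the change score. It rests on the plan's SD of 6, its assumed correlations and one follow-up.
- **Gender, age, BMI.** The gain cannot be computed from the document.

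This should be changed because the change is nearly free and removes an analyst choice. It does not show that the design fails.

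**What to change.** Replace the conditional sentence in Plan for data analysis with:

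> The repeated-measures ANCOVA of endotoxin will include baseline endotoxin and gender as covariates in every case, regardless of observed balance; any further covariates (for example age, BMI) will be fixed before unblinding.

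Add a sentence stating that this model, and not the unadjusted t-test, gives the main endotoxin result.

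The cost is wording. Blood is already drawn at weeks 0, 8 and 26, and gender is known from the stratification, so no new data are needed. The statistical price is one or two degrees of freedom, out of 98 with 100 patients in two groups.
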